**Fig 2 pone.0306408.g002:**
[figure not shown]
The tridirectional relationship between circadian disturbances, mental disease and obesity. Circadian disturbances, mental disease and obesity are associated through a complex network of intermediating factors, each potentially influencing or being influenced by other factors in the network.

Circadian rhythms in humans can be evaluated through various biomarkers, including hormonal peak values and rhythms, daily body temperature changes, and rhythmic gene expression [26]. Since circadian rhythms are closely intertwined with daily routines, measurements taken in laboratories or in-hospital settings may have low ecological validity due to the impact of these artificial environments. Therefore, there is a need for minimally invasive sampling techniques, compatible with daily routines, which can be applied in a real-life setting.

The primary aims of this study are to: (i) To investigate biological markers of disturbed circadian rhythm in free-living adults with obesity and schizophrenia or BD using non-invasive methods and; (ii) to compare biological markers of disturbed circadian rhythm with subjective and objective measures of sleep quality.

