#### Statistical analyses

The four observational groups will be compared on group characteristics of e.g., BMI, body composition, physical function and SES using One-Way Analysis of Variance (ANOVA) or Kruskal-Wallis tests for continuous or ordinal outcomes, and Chi-squared statistics for categorical outcomes as dictated by model assumptions and applying suitable post-hoc analyses as appropriate.

The primary outcome will be analyzed for each study group. Rhythmicity will be assessed by approximating each individual’s 48-hour profiles to a 24 hour cosine wave function in non-linear mixed effects models thereby allowing for the estimation of amplitude, acrophase, and mesor for each group. Derived variables will be compared between groups using the non-obese control group as the reference. Inter-day variability of circadian parameters will be analyzed for each group. Cosine analyses will be individualized relative to participants objectively measured mean sleep offset time.

The same procedure will be used for the secondary measures of rhythmicity i.e. salivary cortisol and melatonin values. In addition, peak values and peak to trough values will be calculated and compared between groups. Wake-to-bed slopes of cortisol will be calculated by subtracting the bedtime sample value from the sample collected immediately upon awakening and divided by the number of hours separating these two samples [31]. Dim light melatonin onset (DLMO) is estimated by comparing evening melatonin concentrations to the mean levels obtained from samples collected during daylight hours. Other potentially rhythmic variables (blood glucose, oral pH and oral temperature) will be visually reviewed for rhythmicity and if applicable analyzed by similar methods.

The correlation between clock gene expression and sleep parameters (e.g., sleep quality, MEQ-category, AHI, and other sleep parameters (S5 File)) will be investigated through Spearman’s rho in correlation matrices. Additional potentially confounding variables will be added to these matrices. This includes variables related to diet, body composition, medication, physical activity and media device usage.

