Significant findings from the correlational matrices will be further evaluated by longitudinal analyses (e.g. linear regression). In these analyses, measures of circadian rhythmicity e.g., acrophase of clock gene expression, will be used as dependent variables. Independent variables will be ‘group allocation’, BMI, gender and age. Variables with an insignificant effect will be skipped from the model. Subsequently, other variables with a potentially confounding influence as identified in the correlational matrix will be added to the model. The most appropriate model will be selected based on the Akaike Information Criterion (AIC), with preference given to the model having the lowest AIC score [32].

In all tests, a p-value below 0.05 is considered significant.

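### The regression that follows up clock-gene/sleep correlations does not name the sleep measure as a predictor, so an adjusted estimate for aim (ii) is not guaranteed

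*Protocol article*

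**What the plan says.** All references are to the protocol article.

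- **Aim.** The Introduction (end of Background) gives two primary aims. The second is "to compare biological markers of disturbed circadian rhythm with subjective and objective measures of sleep quality".
- **First stage.** Under Statistical analyses, the correlation of clock gene expression with sleep parameters (sleep quality, MEQ category, AHI and others) "will be investigated through Spearman’s rho in correlation matrices". Variables on diet, body composition, medication, physical activity and media use are added to the same matrices as possible confounders.
- **Second stage.** Correlations that reach significance go forward to regression. There, "measures of circadian rhythmicity e.g., acrophase of clock gene expression, will be used as dependent variables", and "Independent variables will be ‘group allocation’, BMI, gender and age".
- **Selection.** "Variables with an insignificant effect will be skipped from the model". Further variables that the matrix suggests may confound are then added, and the final model is chosen by AIC, "with preference given to the model having the lowest AIC score". No term is exempted from either rule.

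**The concern.** The regression exists to examine a correlation between a circadian parameter and a sleep measure, yet the stated predictor list does not contain that measure. The coefficient that addresses aim (ii) is therefore neither named as the target nor protected. If the measure enters, it does so alongside diet, activity and screen-time variables, and must compete with them under a criterion meant for prediction.

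The adjusted coefficient matters because of the design. Strength and limitations says that the two psychiatric groups are expected to fall asleep later and sleep longer. If clock gene expression also differs by group, as the study supposes, a rho pooled over all 80 participants can arise from group differences alone. Only an estimate adjusted for group can tell that apart from an association within groups.

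**Working it through.** **Step 1: follow the text for one pair.** Suppose PSQI and the acrophase of one gene correlate with p < 0.05.

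1. The regression is triggered with acrophase as the outcome.
2. The stated predictors are group, BMI, gender and age. PSQI is absent.
3. Insignificant terms are removed.
4. Variables flagged as possible confounders are added. PSQI is in the matrix, so it can enter here, but only in that capacity.
5. The lowest-AIC model is preferred. PSQI stays only if it earns its place.

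At no step is the PSQI coefficient required.

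**Step 2: what AIC demands of one term.** AIC = −2 log L + 2k. Adding a term with one degree of freedom lowers AIC only if the likelihood-ratio chi-square exceeds 2. P(chi-square with 1 df > 2) = 0.157, so a sleep term with an adjusted p-value above about 0.157 is left out.

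**Step 3: omission when group carries part of the correlation.** From the article: N = 80 in four groups of 20, and a screen at p < 0.05. Assumed: a group pattern of 1, 1, 0.3 and 0 (schizophrenia, bipolar, obesity, control), multiplied by a group effect for the sleep measure and another for the outcome; residual SD 1; slope of the outcome on sleep as listed. There were 4,000 runs per row. Among pairs passing the screen, the AIC of group plus sleep was compared with that of group alone.

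| Group effect on outcome / sleep | Slope | Passed screen | Sleep term omitted by AIC |
|---|---|---|---|
| 1 / 1 | 0 | 30% | 75% |
| 1 / 1 | 0.2 | 86% | 29% |
| 0.5 / 1 | 0.2 | 71% | 16% |
| 1 / 1 | 0.4 | 99.6% | 2% |
| 0 / 0 | 0.3 | 70% | 0.3% |

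**Step 4: omission when other covariates compete.** Assumed: a true sleep/clock-gene correlation of 0.2 to 0.3; four candidate covariates correlated with sleep but with no effect of their own; group and two further covariates fixed in the model; AIC over all subsets of the sleep measure and the four candidates; 1,200 data sets per setting. Omission among screened pairs, over repeated runs of this set-up:

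| Covariate–sleep correlation | Sleep measure omitted |
|---|---|
| 0.3 | 3 to 10% |
| 0.5 | 13 to 23% |
| 0.7 | 31 to 38% |

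**Step 5: where inflation comes from.** In the Step 4 set-up at covariate correlation 0.7, for screened pairs:

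| True value | Mean coefficient, sleep forced in, no extra covariates | Mean coefficient when AIC kept sleep |
|---|---|---|
| 0.2 | 0.30 | 0.40 |
| 0.3 | 0.34 | 0.43 |

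For a true 0.2, the screen accounts for 0.30 − 0.20 = 0.10 and AIC selection for a further 0.40 − 0.30 = 0.10. For a true 0.3, the shares are 0.34 − 0.30 = 0.04 and 0.43 − 0.34 = 0.09.

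The plan gives no figure of its own for aim (ii). Its 17 and 16 per group concern t-tests between groups and do not bear on this point.

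**The case against.** **Aim (ii) still has an estimate.** This stands. A reader might infer that aim (ii) could end with no result at all, and the article does not support that. Spearman's rho is computed for the clock-gene/sleep pairs whatever the regression does, and the aim as worded promises no adjusted coefficient. What can be lost is the adjusted estimate.

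**The sleep measure may be implied.** The article says that significant correlations are evaluated further, which makes little sense in a model without the correlated variable. The four named predictors could be a base adjustment set, and the preceding paragraph lists sleep parameters separately from possible confounders. This is a fair reading of intent. The predictor list does not state it, however, and on this reading too the sleep term would still be open to removal by AIC.

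**AIC is a preference.** True, and nothing says that coefficients from rejected models will be withheld. Nothing says that they will be reported either.

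**Forcing the term in does not make the reported set complete or unbiased.** This stands. A reader might blame AIC for all upward bias, but Step 5 shows that the screen causes part of it. The screen also leaves non-significant pairs without any adjusted estimate, and the fix changes neither.

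**The rates rest on assumptions.** This also stands. The documents give no covariate correlations or effect sizes. The simulations keep group in the model and do not imitate the written removal of insignificant base variables.

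**This is detail for an analysis plan.** This does not stand. The article itself fixes the outcome, predictors, removal rule, entry route and selection criterion.

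**Conclusion.** The point holds in a limited form. As written, the follow-up regression does not name the sleep measure as the exposure and does not protect it from selection, so an adjusted estimate for one of the two primary aims is not guaranteed. The unadjusted correlation remains, but pooled over groups expected to differ in sleep it cannot show whether an association goes beyond group.

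Under the assumptions shown, the sleep term is omitted in anything from almost none to about a third of screened pairs with a true association, and in about three quarters when group explains the whole crude correlation. In that last case the small adjusted coefficient with its interval is the informative result, so it should be shown. The rates illustrate what the rule can do; they do not forecast this study. The conclusion itself rests on the text and not on them.

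This is worth correcting before analysis. It does not affect the primary outcome comparison between groups.

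**What to change.** In the regression paragraph of Statistical analyses:

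- Name the sleep measure under study as the exposure in each follow-up regression.
- Exempt it from both the removal of insignificant terms and the AIC selection.
- Report its coefficient with a 95% confidence interval whatever the result.
- If AIC is kept, let it choose only among additional covariates.

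The cost is one or two sentences, with no new data and no change to the sample size. The downside is that some models will carry a term that does not lower AIC. Because regressions would still run only for pairs passing the Spearman screen, the report should say that these coefficients come from screened pairs and may be too large for that reason.

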#### Hair follicle clock gene expression

All hair follicles are analyzed at Steno Diabetes Center Odense, Odense, Denmark. After collection during home visits the samples are stored at -80° C until further analysis. RNA from the hair follicles is isolated using an RNeasy Micro kit (QIAGEN, Hilden, Germany) according to the manufacturer’s instructions. Briefly, the samples are thawed on ice after which they are centrifuged to precipitate the hair follicle cells. After removing the supernatant, the cells are lysed using a RLT buffer supplemented with DTT. The lysates are then processed through spin-columns, treated with DNase (Qiagen, Denmark) to remove genomic DNA, washed with RW1 and RPE buffers, and subjected to ethanol precipitation. The final RNA is then eluted in a minimal volume of RNase-free water and quantified by NanoDrop spectrophotometer (Thermo Fisher Scientific, Waltham, MA). RNA is reverse transcribed to cDNA using a high-capacity cDNA reverse transcription kit (Applied Biosystems, Foster City, CA) according to manufacturer’s protocol. The qPCR is performed on a QuantStudio 5 real-time PCR system (Applied Biosystems, Foster City, CA) using the pre-designed commercially available TaqMan Custom Arrays (Applied Biosystems, Foster City, CA). All samples are run in triplicates. We will test the gene expression of a panel of circadian rhytm-related genes (e.g. *PER3*, *NR1D1/2*). The expression of any genes of interest will be normalized to appropriate reference genes. We will test a panel of reference genes to identify the most appropriate and stable candidates.

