#### Main outcomes

The primary outcome is circadian expression of clock-genes, the secondary outcomes are circadian salivary cortisol and melatonin rhythms.

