#### Power calculation

Based on Sun et al. (2016) [12], and targeting a statistical power of 0.8 and an alpha error of 0.05, our study requires groups of 17 participants for the mesor and 16 participants for the amplitude to show statistically significant group differences in clock gene expression, as measured by unpaired t-tests.

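### The primary outcome is a family of nine tests per gene over an open gene panel, every test is judged at 0.05 without adjustment, and the stated power is per test and omits acrophase

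*Protocol article*

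**What the plan says.** - **Primary outcome** (Main outcomes): "The primary outcome is circadian expression of clock-genes". This is a class of measurements; no gene is singled out.
- **Genes** (Hair follicle clock gene expression): "We will test the gene expression of a panel of circadian rhytm-related genes". PER3 and NR1D1/2 are given only as examples, so the number of genes is open.
- **Parameters and contrasts** (Statistical analyses): a 24-hour cosine is fitted in non-linear mixed models to give amplitude, acrophase and mesor. These are compared between groups with the non-obese controls as reference. With four groups that is three contrasts.
- **Significance rule** (last sentence of Statistical analyses): "In all tests, a p-value below 0.05 is considered significant". The section's only mention of post-hoc procedures concerns the comparison of group characteristics.
- **Power** (Power calculation): for power 0.8 at alpha 0.05, the requirement is put at "groups of 17 participants for the mesor and 16 participants for the amplitude". The test assumed is the unpaired t-test, and neither the gene nor the pair of groups is named. No effect size or standard deviation is given; a published study is cited instead.
- **Group size** (Methods): 80 participants, 20 per group.

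**The concern.** A study that designates a primary outcome, with an alpha and a power for it, leads the reader to expect one controlled error rate for that outcome. Here the outcome is a set of tests whose size is not fixed, and the plan says that any of them below 0.05 counts. Followed literally, the study could report a significant primary finding because it had many chances to find one. Nothing in the text says which gene, parameter or patient group would carry the conclusion.

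The effect can carry forward. The correlation matrices of clock-gene expression with sleep and other variables fall under the same rule, and their significant entries are what go on to regression.

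The power statement does not match this family. It covers one test at a time at unadjusted 0.05, and it leaves out one of the three parameters that are compared.

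**Working it through.** **Inputs from the article.** Alpha 0.05 per test; 3 parameters; 3 contrasts sharing one control group; 20 per group; stated n of 17 (mesor) and 16 (amplitude) at power 0.80.

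**Assumptions, because the article does not give them.** The number of genes; the correlations between genes and between parameters; two-sided tests; one pairwise t-test per contrast; all null hypotheses true for the error rates.

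**1. The plan's own figure.** The 17 and 16 cannot be reproduced forwards without an effect size and SD. Solving backwards with the noncentral t distribution (two-sided 0.05, power 0.80) gives the standardised differences they imply:
- n = 17 (mesor): d = 0.99
- n = 16 (amplitude): d = 1.02

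This is circular. It shows what the sample sizes imply and does not confirm them.

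**2. Number of primary tests.** 3 parameters × 3 contrasts = 9 per gene, so 9G for G genes.

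**3. Chance of at least one p < 0.05 when nothing differs.** If all tests were independent, this is 1 − 0.95^(9G). Contrasts that share a control group are not independent, so the rate was also simulated with 20 per group, a shared control, and several assumed correlations. The last column runs from strong correlation (genes 0.7, parameters 0.5) to none.

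| Genes | Tests | Independent tests | Simulated, shared control |
|---|---|---|---|
| 1 | 9 | 1 − 0.95^9 = 37.0% | 29–33% |
| 3 | 27 | 1 − 0.95^27 = 75.0% | 54–71% |
| 10 | 90 | 1 − 0.95^90 = 99.0% | 80–98% |

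One gene and one parameter, with only the three contrasts, already gives 12–13% in simulation (14.3% if independent).

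**4. Power at the planned 20 per group, for the implied effects** (noncentral t; mesor / amplitude):

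| Alpha per test | Power |
|---|---|
| 0.05 | 0.86 / 0.88 |
| 0.05/3 (three contrasts) | 0.73 / 0.76 |
| 0.05/9 (one gene) | 0.58 / 0.62 |
| 0.05/27 (three genes) | 0.43 / 0.47 |

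**5. Detectable difference at 20 per group with 80% power.** d = 0.91 for one test at 0.05; d = 1.06 if three contrasts share alpha equally.

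**6. Source of the effect size.** The study cited for power is reference 12. The Background cites it within a group of three references (11–13) on schizophrenia, covering skin fibroblasts, white blood cells and post-mortem prefrontal cortex. None of these tissues is hair follicle. The text does not say which tissue belongs to which reference.

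**The case against.** **It is an exploratory observational study.** The design is case-control, the aims are to investigate and compare, and no treatment is tested. Each patient group also poses its own question, so adjusting across the three contrasts is debatable. This stands as an argument for leaving the method open: a defined family with false discovery control, or an exploratory label, would do as well as a single named test. It does not rescue the present text, which names a primary outcome with alpha and power and does not call the results exploratory.

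**The detail may be in an analysis plan that is not shown.** A gene hierarchy or an adjustment is often placed there, and 0.05 can be applied to adjusted p-values. That is possible. The article is not merely silent, however: it states a rule for all tests without qualification. If an unseen plan adjusts, this sentence still needs to be aligned with it.

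**Stronger readings that the text does not support.**
- A reader might take the three example genes as the panel and quote a single false-positive rate of roughly two in three. The genes are only examples and no correlations are given, so that is one scenario among several. A different test from the mixed model would also change the numbers.
- A reader might conclude that the power statement concerns a single unidentified test. It gives two calculations and names mesor and amplitude; what is unnamed is the gene and the group pair.
- A reader might call the study underpowered. For one unadjusted test, 20 per group exceeds 17 and 16 and gives 0.86/0.88 for the implied effects if everyone is analysable.
- A reader might add that the cited power study did not involve people with obesity. The article does not report that study's BMI, so nothing can be said.

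**Conclusion.** The point holds and should be fixed. The primary outcome is nine tests per gene over a panel of unstated size, with an explicit unadjusted 0.05 rule and no primary gene, parameter or contrast. If no group differs, at least one significant primary result is expected with a probability of about 29–37% for one gene, 54–75% for three and 80–99% for ten. The ranges rest on pairwise tests and on assumed correlations, from strong correlation up to full independence. The conclusion does not depend on the exact figure: even the lowest value is almost six times the nominal 5% (29/5 = 5.8), and the article plans more than one gene.

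On power the point is narrower. The stated 0.8 is a per-test figure at unadjusted 0.05 for mesor or amplitude, and acrophase has none. For the implied effects, power at 20 per group falls below 0.8 once the three contrasts share alpha. That the effect size does not come from hair follicles is an inference from the tissues listed in the Background.

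**What to change.** Before any group-labelled expression data are seen:

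1. Either name one gene, one parameter and one contrast as the primary test at 0.05, or list the primary gene × parameter × contrast family and control it by Holm or Benjamini-Hochberg.
2. Apply false discovery rate control to the remaining comparisons and to the correlation matrices, or label them exploratory.
3. Replace the blanket 0.05 sentence with wording that says where 0.05 applies unadjusted and where it applies to adjusted p-values.
4. Restate power as per test: 20 per group has 80% power for d = 0.91 in one test, and for d = 1.06 if three contrasts share alpha. State the effect size used, that it was not derived from hair follicles (if the authors confirm this), and that acrophase is not powered.

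**Cost.** Wording only; no added participants, samples or procedures. Power becomes less favourable for everything except a single named test, which keeps 0.86 (mesor) or 0.88 (amplitude) for the implied effects. If the choice is made after the group comparisons are known, it can no longer pass as prespecified.

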## Discussion

This study has the potential to significantly advance circadian rhythm assessment by implementing multiple self-sampling techniques in Scandinavian cohorts of people with diverse mental health statuses and varying degrees of obesity. Hair follicle sampling, as highlighted in a recent literature review by Crnko et al. (2021), offers high-quality RNA extraction with minimal invasiveness, presenting a promising technique for clock gene expression analysis [26]. The application of this method in a Scandinavian demographic is particularly notable, as previous research has primarily concentrated on Asian populations, which exhibit hair characteristics distinct from Caucasian populations [33].

Furthermore, the comparative analysis of self- versus professionally-assisted sampling and collection of participant experiences within our study will yield comprehensive insights into the practicality of this method. Such information is vital to assess the wider applicability and feasibility of hair follicle sampling across various demographic groups.

Previous research has identified circadian disturbances, marked by altered clock gene expression, as factors in various somatic and mental diseases. These range from obesity [23–25], OSA [34], type-2 diabetes [35], leukemia [36], mood disorders [37], major depressive disorder (MDD), schizophrenia and BD [38–40]. Interestingly, in a recent study designed to evaluate cross-disorder polygenic risk scores for chronotype, sleep duration and insomnia across BD, MDD, and schizophrenia, there was a genetic overlap in all three disorders with each trait [41]. Despite this, no study to date have allowed for a direct group comparison of rhythmic clock gene expression between these diagnoses. Furthermore, no study has assessed the comorbid effect of obesity and mental disease on clock gene expression.

